### Research team

This study will involve 7 physiotherapists; 1 Clinical physiotherapist with more than 10 years of experience in the use of dry needling for MTrP treatment, 2 evaluator physiotherapists and 2 physiotherapists responsible for carrying out the manual physiotherapy and therapeutic exercise treatment of the participants, one physiotherapist responsible for the interview, initial screening and randomization of participants, and one physiotherapist who will perform the statistical analysis.

### Sample size

The pain variable is chosen as the primary measurement of the study results. An effect size TE = 0.25 will be considered [21]. A correlation between repeated measures of 0.5 shall be assumed. Assuming the performance of 6 measurements -basal and a week after the dry needling, and post-treatment: at one week, at one month, at 3 months and at 6 months- in two treatment groups, sphericity correction will be determined at 0.5. With a statistical power of 0.95, with an alpha level of 0.05, a total sample size of 28 patients is estimated, and taking into account 25% for losses, a total of 36 patients needs to be reached, being 18 in both groups, using the Software Gpower 3.0.18 [22].

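### The inputs stated for the sample size do not give 28 patients: with a sphericity correction of 0.5 the repeated-measures F test needs 46, and 28 give power of about 0.78, not 0.95

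*Protocol article*

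**What the plan says.** All the figures are in one paragraph, the Sample size section of the protocol article. Pain is the primary variable. The inputs are:

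- effect size: "An effect size TE = 0.25 will be considered"
- correlation: "A correlation between repeated measures of 0.5 shall be assumed"
- number of measurements: "Assuming the performance of 6 measurements" (baseline, one week after needling, and four post-treatment visits)
- groups and nonsphericity: "in two treatment groups, sphericity correction will be determined at 0.5"

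The result is "With a statistical power of 0.95, with an alpha level of 0.05, a total sample size of 28 patients is estimated". It is then raised for attrition: "taking into account 25% for losses, a total of 36 patients needs to be reached, being 18 in both groups". The software named is G*Power 3.0.18. The paragraph does not say which F test was selected.

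**The concern.** The paragraph prints every input that G*Power asks for in a repeated-measures ANOVA, so the result can be checked directly. A sphericity correction of 0.5 halves both the noncentrality parameter and the degrees of freedom, which should raise the required number well above the value under sphericity. Yet 28 is the value under sphericity.

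What is at stake is the justification for the size of the trial on its primary outcome. The protocol states a 5% risk of missing the planned effect. If its own assumptions imply a risk of 11% to 23%, readers are told that the design is more sensitive than it is, and a null result could be given more weight than it deserves.

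**Working it through.** **Inputs (all from the Sample size section).** f = 0.25 (read as Cohen's f, the G*Power metric), rho = 0.5, m = 6 measurements, k = 2 groups, alpha = 0.05, target power 0.95, epsilon = 0.5.

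**Formula.** G*Power repeated-measures ANOVA, within-between interaction, noncentral F:

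- lambda = f² × N × m × epsilon / (1 − rho)
- df1 = (k − 1)(m − 1) × epsilon
- df2 = (N − k)(m − 1) × epsilon

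With the stated f, m and rho, f² × m / (1 − rho) = 0.0625 × 6 / 0.5 = 0.75, so lambda = 0.75 × N × epsilon.

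**Step 1: reproduce the printed 28.** This works with epsilon = 1.0 and everything else as stated:

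- N = 26: lambda = 19.5, df 5 and 120, power 0.936
- N = 28: lambda = 21.0, df 5 and 130, power 0.954

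The smallest even N that reaches 0.95 is 28, the printed figure.

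**Step 2: use the stated epsilon of 0.5.**

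| N | lambda | df1, df2 | power |
|---|---|---|---|
| 27 (36 less 25%) | 10.125 | 2.5, 62.5 | 0.768 |
| 28 (stated requirement) | 10.5 | 2.5, 65 | 0.785 |
| 36 (no loss) | 13.5 | 2.5, 85 | 0.888 |
| 44 | 16.5 | 2.5, 105 | 0.945 |
| 46 | 17.25 | 2.5, 110 | 0.954 |

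The smallest even N for 0.95 is 46. If that number had to survive a 25% loss, 46 / 0.75 = 61.3, or 62 randomised.

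**Step 3: could another reading of the stated inputs give 28?**

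- Within-factor test, epsilon 0.5: 46
- Between-factor test: 124, whatever the epsilon
- Alternative effect-size conventions, epsilon 0.5: 108 to 110
- Epsilon applied to the degrees of freedom but left out of lambda: 24
- Five or ten measurements instead of six, epsilon 0.5: 52 or 32

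None returns 28.

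**Step 4: which single changed input would give 28?** Three would: epsilon = 1.0; rho = 0.7 with epsilon kept at 0.5; or f of about 0.32 to 0.33 with epsilon kept at 0.5. Each contradicts a value the paragraph states.

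**Step 5: the loss allowance, taking 28 as given.** 28 × 1.25 = 35, and 36 is the next even number. Allowing for a 25% loss means dividing: 28 / 0.75 = 37.3, or 38 with equal groups. From the other side, 36 × 0.75 = 27, one below 28; at epsilon = 1.0, 27 completers have power 0.945. The loss that leaves exactly 28 of 36 is 1 − 28/36 = 22%.

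**The case against.** The mismatch itself has no good answer: it follows from printed numbers, and the likely alternative readings do not remove it. Four objections limit what may be concluded from it.

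*The cause is not shown.* A reader might infer that the correction was certainly left out. The article contains no software output, and a misreported correlation or effect size would also explain 28. Epsilon = 1.0 is the most economical explanation, because it is a natural round value and reproduces 28 with nothing else changed, but it remains an inference. This objection stands.

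*The test is not named, and it may not be the one that compares the groups.* A reader might infer that the trial's real power to detect a treatment effect is 0.78. The document does not support that. In the Statistical analysis section, repeated-measures ANOVA is applied within each group separately. The groups are compared on change from baseline with a t test or Mann-Whitney test, and an ANCOVA is also mentioned. The 0.78 belongs to the repeated-measures F test implied by the sample-size inputs. It corrects the stated 0.95 on its own terms and says nothing about the power of the change-score comparison. This objection also stands, and the restated power must therefore name its test.

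*Twenty-eight completers is not the only case.* The trial randomises 36 and declares intention to treat. If all 36 are analysed, power is 0.888. That is fair, but it is still below 0.95.

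*The loss allowance is a trivial matter.* A reader might treat it as a second serious error. It amounts to one completer, and to a change in power from 0.954 to 0.945 at epsilon = 1.0. It also has meaning only if 28 is the right requirement. At epsilon = 0.5, 36 patients fall short of 0.95 before anyone is lost, so saying that 36 tolerates 22% loss would be wrong there.

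It cannot be said that this detail is left to a fuller document. Nothing is missing: the article prints a complete calculation, and its parts do not agree.

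**Conclusion.** Wrong as written. The stated inputs and the stated 28 cannot both be right. Under the stated inputs, 46 evaluable patients are needed for 0.95 power. The planned 36 give 0.768 with the anticipated 25% loss and 0.888 with none, so the risk of missing the planned effect is about 23% (1 − 0.768) or 11% (1 − 0.888), against the stated 5%.

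This rests on two assumptions: that 0.25 is Cohen's f in the G*Power metric, and that the test is one of the repeated-measures F tests that use epsilon. The second is well supported, since the paragraph specifies a sphericity correction, and both such tests give the same answer. Failure to enter the correction is the probable cause but is not established. The shortfall in the loss allowance is a minor side point that applies only if epsilon was in fact 1.0.

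**What to change.** Keep 36 and name the test to which the power refers. Then do one of the following, according to what was entered in the software.

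(a) If epsilon = 0.5 is the intended assumption, restate the power along these lines: for the repeated-measures group-by-time F test with epsilon = 0.5, 36 randomised patients give about 77% power for f = 0.25 with 25% loss, and 89% with no loss. Drop the claim that 28 suffice for 0.95.

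(b) If epsilon = 1.0 was entered, correct the stated 0.5 to 1.0 and justify assuming sphericity across visits that run from baseline to six months after treatment. Only in this case, also change the loss allowance to about 22%, since 36 less 25% leaves 27 (power 0.945).

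If a different input turns out to be misreported, correct that value instead and show the calculation.

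The cost is a rewrite of one paragraph. Under (a) the stated power becomes less favourable; under (b) an assumption has to be defended. No patients, visits or analyses change.

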### Randomization and blinding

At baseline, the non-interventionist physiotherapist, through the Random Allocation Software, will randomize by permuted blocks [4, 8], the participation of the 5 intervening physiotherapists with respect to a sample of 36 participants. The physiotherapist in charge of performing dry needling –which may be A (experimental) or B (control)- and 2 groups of 2 physiotherapists, G1 and G2, with an evaluator and a therapist in each group. 4 possible treatment groups (AG1, AG2, BG1, BG2) will be obtained evenly in each randomization block.

Participants who successfully pass the phone screening will be assigned a number on the randomization table in order of inclusion in the study; the treatment group (A or B) and physiotherapist group (G1 or G2) in which they will be included are specified. The physiotherapist responsible for carrying out the dry needling, will provide a list with the names of the participants, showing the type of intervention that each will receive (A or B).

Each participant will receive a single dry needling or sham dry needling intervention at the start of the first treatment session, conducted by a physiotherapist with more than 10 years of experience in MTrP treatment with dry needling. Said physiotherapist will be blinded to the baseline data of participants. On the other hand, both the physiotherapists who evaluate the participants and those who perform manual physiotherapy treatment and therapeutic exercise, will be unaware of the group of each participant.

In addition, data collected during the assessment of participants will not be revealed to the physiotherapists who perform the treatment, and participants will be instructed not to disclose their experience and information related to the first treatment session of dry needling.

Lastly, the physiotherapist responsible for the statistical analysis will be blinded. Once the intervention is finished he will receive a data table in excel with all the necessary data in binary code.

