### Statistical analysis

Data analysis will be carried out following the evaluation standards of the design of experimental studies with a control group. The experimental group (dry needling + manual physiotherapy and therapeutic exercise) will be compared with the control group (sham dry needling + manual physiotherapy and therapeutic exercise).

Data will be analysed using SPSS v.22 software for Windows. All statistical tests will be carried out considering a confidence interval of 95% (*p*-value <0.05) to determine the effectiveness of the 2 interventions by the method of intention to treat. Prior to statistical comparisons, all data will be analysed to determine the distribution of normality by the Shapiro-Wilk test. Subsequently, the homogeneity of the two intervention groups will be studied using Student’s t test for independent samples for data conforming to normal and the Mann-Whitney test for data that do not. The sex variable will be studied through Pearson χ2 or Fisher’s exact test, if the former cannot be used. Then a descriptive analysis of the data for the dependent variables will be performed. In these analyses, the mean and standard deviation (SD) for the dependent variables with normal distribution will be calculated. For variables that do not conform to normal, the data will be expressed with the median and first and third quartiles.

For the sex variable, frequencies are used. The existence of differences within each group will be determined, taking into account each group in isolation, between the different measurements (baseline and one week after dry needling; and post-treatment: at one week, at one month, at 3 months and at 6 months) in each of the study variables. In the VAS variable, measurements will also be taken in the treatment sessions; 2nd week, 3rd week, 4th week, 5th week, 6th week, using ANOVA for repeated measures, supplemented with simple and Helmert-type contrasts for variables that follow normal or Friedman’s ANOVA test, supplemented by Dunn’s multiple comparison test for those variables that will not conform to normal. ANCOVA will be performed to see the effect through different analyzes of the results and to intensify statistical power of the study. For this, the existence of a linear relationship and the homogeneity between the crude and basal scores of the dependent variables will be previously studied.

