For comparison between groups, a variable that we define as “difference” will be found; for each dependent variable, by subtracting the baseline measurement - at one week following needling, baseline - post 1 week, baseline - post 1 month, baseline - post 3 months and baseline - post 6 months (for the DASHe variable, the measurement will not be collected at one week after needling).

For the VAS variable, the “difference” variables will be found between baseline - week 2, week 3, week 4, week 5, week 6. To determine differences in dependent variables between the two intervention groups, the Student t test will be applied for related samples in variables whose data follow normal, in this case the effect size will be calculated according to the formula d = 2 t/√g. In the case of variables whose data do not follow normal, an analysis by the Mann-Whitney test will be performed and the effect size will be estimated according to Grissom procedures according to the formula.

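### Arm is balanced on physiotherapist team (G1/G2) in every randomisation block, but the stated between-arm tests leave team out, which costs some precision if the teams differ

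*Protocol article*

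**What the plan says.** Randomization and blinding forms "2 groups of 2 physiotherapists, G1 and G2, with an evaluator and a therapist in each group". The physiotherapist who handles allocation "will randomize by permuted blocks [4, 8"; I read the bracketed numbers as block sizes. The section then states that "4 possible treatment groups (AG1, AG2, BG1, BG2) will be obtained evenly in each randomization block". Each participant receives a number in the randomisation table, which fixes both the arm (A or B) and the team (G1 or G2).

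Statistical analysis forms a change from baseline for each outcome and time point. "To determine differences in dependent variables between the two intervention groups", it says, "the Student t test will be applied for related samples in variables whose data follow normal"; for the remaining variables, "an analysis by the Mann-Whitney test will be performed". It also says that "ANCOVA will be performed to see the effect through different analyzes of the results and to intensify statistical power of the study". The only covariate that can be inferred for this ANCOVA is the baseline value, because a linear relationship and "homogeneity between the crude and basal scores of the dependent variables will be previously studied". Team, evaluator, therapist and block do not appear in the section. The sample size section likewise assumes two groups and no team factor.

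**The concern.** When allocation is forced to be even across a factor, chance imbalance on that factor no longer contributes to the error of the treatment difference. A test that ignores the factor still counts its variation as noise. The reported standard error is then larger than the true one, intervals are too wide and the test rejects too seldom.

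The factor could plausibly matter here. Each therapist gives six weekly sessions of about 45 minutes of manual treatment plus about 25 minutes of supervised exercise, so a difference between the two therapists could show in the change of any outcome, including the VAS. In a trial of 36 participants that allows for 25% losses, precision that the randomisation has already secured should not be given away.

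**Working it through.** **Inputs.** From the document: 36 participants, 18 per arm, two teams, and equal arm-by-team cells in each block. Since 36 / 4 = 9, a complete table has 9 per cell. From Statistical analysis: between-arm tests on change scores without team. The document gives no figure for a team effect, so none can be reproduced. The team difference τ, in units of the within-cell SD of the analysed change, is my assumption, with range 0 to 1.0. I treat the t test as one for independent samples, since the arms are different people; its related-samples wording is a separate matter. So is the question whether the stated sample size follows from its inputs: only the total of 36 is used here.

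**Estimate.** Each arm has 9 participants from each team, so the team effect cancels in A minus B. There is no bias, and the true standard error is √(2/18) = 0.333 SD whatever τ is.

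**Reported standard error without team.** The team difference adds 9·9/18·τ² = 4.5τ² to the sum of squares within each arm, so 9τ² over both arms on 36 − 2 = 34 degrees of freedom. The expected residual variance is 1 + 9τ²/34 = 1 + 0.265τ², and the standard error is too large by about √(1 + 0.265τ²):

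- τ = 0.25: √1.017 = 1.008
- τ = 0.5: √1.066 = 1.033
- τ = 1.0: √1.265 = 1.125

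**Simulation.** 40,000 runs per setting, normal data, 9 per cell, comparing the two-sample t test with a linear model of arm plus team (no baseline term in either). Power is for an illustrative effect of 1 SD.

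| τ (assumed) | Type I error, without / with team | 95% CI half-width (SD), without / with team | Ratio of half-widths | Power, without / with team |
|---|---|---|---|---|
| 0 | 0.050 / 0.050 | 0.673 / 0.673 | 1.00 | 0.83 / 0.83 |
| 0.25 | 0.047 / 0.049 | 0.678 / 0.673 | 1.01 | 0.83 / 0.83 |
| 0.5 | 0.044 / 0.050 | 0.694 / 0.673 | 1.03 | 0.81 / 0.83 |
| 1.0 | 0.028 / 0.050 | 0.757 / 0.673 | 1.12 | 0.76 / 0.83 |

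The simulated ratios agree with the formula. With 28 participants (7 per cell) they are much the same: 0.795/0.771 = 1.03 at τ = 0.5 and 0.867/0.770 = 1.13 at τ = 1.0.

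**Scale.** With two equal teams, team explains (τ²/4)/(1 + τ²/4) of the variance: 0.0625/1.0625 = 6% at τ = 0.5 and 0.25/1.25 = 20% at τ = 1.0.

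**Where a team difference can enter.** Team is assigned once, which implies that the same evaluator sees a participant throughout. A constant evaluator offset then cancels in baseline minus follow-up. The VAS is marked by the participant. What remains is mainly the therapist's influence on change, plus any evaluator difference that varies with time or with the level measured.

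**The case against.** The strongest reply is that this is a condensed article and a full covariate list belongs in the analysis plan. That stands in part for the ANCOVA: the article describes only baseline scores for it, but does not exclude other terms. It does not stand for the t and Mann-Whitney tests, which are named as the between-arm comparison and, as specified, have no place for team.

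A second reply is that team is not a patient characteristic. Participants are randomised to it, so G1 and G2 participants differ at baseline only by chance, and only what the teams themselves cause can matter. That is correct, and it limits the likely size.

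A reader might also infer more than the documents support:

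- *That the teams are known to differ.* No between-team or between-evaluator figure is given. Physiotherapist training plans consensus training in treatment and measurement and an external observer of similarity, and Tables 1 and 2 fix the content of treatment.
- *That the examiner-measured outcomes (goniometry, dynamometry, algometry) lose most.* A constant evaluator offset drops out of the change scores, so this is not shown.
- *That the inference is invalid.* The error is on the conservative side: no bias, and type I error at or below 5%.

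**Conclusion.** The mismatch is real: the randomisation balances arm on team in every block, and the between-arm analysis as stated does not use team. The consequence is lost precision only, and its size depends on a team difference that the documents do not give. It is negligible at 0.25 SD, small at 0.5 SD and noticeable at 1.0 SD, and a difference as large as 1.0 SD has no support in the document. The figures assume equal cells, normal data and the same team difference in both arms. The point is worth acting on because the correction costs almost nothing, not because a large loss has been shown.

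**What to change.** Make the planned ANCOVA the between-arm analysis for the VAS and the secondary outcomes, with arm, baseline score and team (G1/G2, fixed factor) as terms. Where a rank test is needed, stratify it by team, for example a van Elteren test on the change scores; a fixed factor cannot simply be added to a Mann-Whitney test. Team should be in the ANCOVA even if evaluator offsets are constant: with a baseline slope b, a share 1 − b of such an offset remains in the adjusted score, so it cancels fully only when b = 1.

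This replaces the simple t and Mann-Whitney tests as the between-arm comparison, rather than adding a term to them. It costs one degree of freedom; at no team difference the simulated half-width is 0.673 SD either way. No new data are needed, since team is in the randomisation table. The coded data table sent to the blinded analyst must carry a team column, which does not reveal the arm.

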## Methods

### Design

Study protocol for a randomized controlled parallel group single-blind trial. This study was registered with the International Standard Randomized Controlled Trial Number (ISRCTN30604244) and complies with the recommendations of The SPIRIT 2013 Statement.

Participants will be randomized to receive dry needling, either real or sham. Allocation to either group, namely real or sham dry needling, will be achieved through a computer-generated sequence of random numbers. The allocation sequence is created and carried out by a non-interventionist physiotherapist, in charge of telephone screening and of handling the data obtained in the various assessment sessions.

Figure 1 shows a flowchart of the progress of the various stages of this test. This study was approved by the Committee on Human Research, Universidad de Alcalá (Reference: CISM/HU/2015/19).

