### Participants

From the town of Alcalá de Henares (Madrid), aged between 18 and 65 years with chronic mechanical shoulder pain of unspecific origin, lasting at least 3 months and provided they give their consent after being informed about participation in the study. The recruitment of participants will be conducted via email for University of Alcalá workers and students and by placing posters in a number of social and sports centres around the city of Alcala de Henares, where information about the study and contact information will be provided. Subsequently, a first telephone interview will be conducted to clarify any doubts of the participants, and the first screening for inclusion in the study will be carried out.

Participants’ personal data will be numerically coded and stored in a computer database, which may only be accessed to by the physiotherapist in charge of participant randomization and blinding.

Informed consent, as well as all study information will be emailed to the participants. Subsequently, prior to data collection and baseline measurement, participants should sign the informed consent, which could be revoked at any time during the intervention.

Inclusion criteria:Chronic mechanical shoulder pain of unspecific origin lasting at least 3 months.Aged between 18 and 65 years.Presence of active trigger points or areas of mechanical hypersensitivity in the muscles to be treated (upper trapezius, infraspinatus, subscapularis and middle deltoids) with pain reproduced in one or more muscles.

Participants will be examined for the presence of active trigger points in the muscles selected by a clinician with more than 10 years of experience in the treatment of MTrPs. Diagnosis of MTrPs will be determined by the presence of the following criteria: [1] hypersensitive point in a palpable taut band, [2] visible or palpable local spasm in response to MTrP palpation, and [3] reproduction of referred pain by palpation of the sensitive spot. These criteria have shown good interexaminer reliability (κ, kappa between 0.84 to 0.88) when applied by an experienced evaluator [20].

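### The physiotherapist who decides the phone screen also creates and runs the allocation sequence, and the arm is tied to passing that screen, so the next assignment is open to the recruiter and exclusions can follow allocation

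*Protocol article*

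**What the plan says.** All references are to the Protocol article.

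- **Who holds the sequence.** The Design section states: "The allocation sequence is created and carried out by a non-interventionist physiotherapist, in charge of telephone screening and of handling the data obtained". The Research team section lists "one physiotherapist responsible for the interview, initial screening and randomization of participants".
- **When the number is given.** Randomization and blinding: "Participants who successfully pass the phone screening will be assigned a number on the randomization table in order of inclusion in the study".
- **What the number fixes.** The same sentence continues: "the treatment group (A or B) and physiotherapist group (G1 or G2) in which they will be included are specified". Each physiotherapist group has its own evaluator and its own therapist.
- **What is still open after the call.** The Participants section describes the telephone interview as a first screen only. On consent it says that "prior to data collection and baseline measurement, participants should sign the informed consent". On the trigger-point criterion it says: "Participants will be examined for the presence of active trigger points in the muscles selected by a clinician".
- **Analysis.** The Statistical analysis section commits to intention to treat.

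**The concern.** Two protections of a randomised comparison are at stake.

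The first is concealment. Whoever decides on entry should not be able to know the next arm. Here the person who judges the telephone screen is the person who made the list and applies it. Knowledge of the next entry could affect, even unintentionally, how a borderline caller is judged or when a caller is entered.

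The second is the order of steps. If the arm is fixed once the call is passed, the trigger-point examination and signed consent come afterwards. A participant who fails the one or declines the other has already been allocated. Such losses need not be balanced between arms, and they remove people from the set that intention to treat is meant to keep whole.

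The trial is small and its main outcome is pain marked by the participant, so a few selectively admitted or lost participants could matter. No later analysis can restore concealment.

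**Working it through.** The point is procedural and the plan gives no figure for it, so the check is a comparison of sections.

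**Step 1: who can know the next arm.** Design and Research team agree that one role covers the telephone interview, the screening decision, the making of the sequence and its application. Randomization and blinding describes blinding for the evaluators, the treating therapists and the analyst, and keeps baseline data from the needling physiotherapist. None of these measures covers the recruiter. Computer generation and permuted blocks describe how the sequence is produced, not how it is concealed.

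**Step 2: what the call can settle.** Age, duration of pain and history can be asked by telephone. The trigger-point criteria in the Participants section cannot: a palpable taut band, a local spasm on palpation, and referred pain reproduced by palpation. Signed consent is also still outstanding.

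**Step 3: what can happen in between.** Taking Randomization and blinding literally, the order is call, number with arm and team, then consent and examination. A failed examination or a refusal then follows allocation.

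**Step 4: the consequence for intention to treat.** Consent precedes all data collection, so a numbered participant who refuses has no data at all, not even baseline. That participant cannot be analysed as allocated. The article does not say how such people are counted or whether their numbers are reused.

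**Step 5: wording that points the other way.** The abstract describes people who meet the inclusion criteria and are then randomised. Randomization and blinding opens by placing randomization at baseline, and the sentence on numbers refers to order of inclusion. These would fit assignment after eligibility is confirmed. They do not fit a number that follows from the call, so the sections conflict or are at best ambiguous.

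**Step 6: scale.** As a yardstick, consider someone who knows the block size and all earlier arms but does not hold the list. With n participants per arm in a block, each A comes after all n of the B's with probability 1/(n + 1), and the same holds for each B. The expected number of assignments that can be deduced with certainty is therefore 2n/(n + 1) out of 2n, a share of 1/(n + 1). If the bracketed 4 and 8 after the mention of permuted blocks are block sizes (the article uses the same bracket style for references):

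- block of 4, n = 2: 1/3 = 33%
- block of 8, n = 4: 1/5 = 20%

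A person who holds the list can look up every assignment. With 36 participants in two groups of 18, one participant is 1/18 = 5.6% of an arm.

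**The case against.** **The order is inferred.** No section sets out number, consent and examination as one explicit sequence. Passing the call may be a condition for receiving a number rather than the moment at which it is given. The wording in step 5 supports this, and the flowchart is not shown. This stands in part: the documents support saying that exclusions and refusals *can* follow allocation, not that they do.

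**A concealment device may be in the full protocol.** A journal article condenses, and envelopes or a locked list may be described elsewhere. A reader might infer from the silence that allocation is definitely unconcealed and that the recruiter predicts every arm. The documents do not go that far; nothing says that the recruiter consults the next entry when judging a caller. But the finding does not rest on a missing detail. The combination of roles is stated twice, and a device handed to others does not by itself conceal a list from the person who made it.

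**Three stronger readings are tempting and should not be drawn.**

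- A reader might infer that the examiner for eligibility is the needling physiotherapist, because the only team member listed with matching experience is "1 Clinical physiotherapist with more than 10 years of experience in the use of dry needling for MTrP treatment". The Participants section says only that a clinician examines. No experience is given for the other members, and the needling physiotherapist is said to be blinded to baseline data. The identity is not shown. The sentence on the named list of arms gives no date, so it does not show that the examiner knows the arm either.
- A reader might infer that outcome data are compromised because the holder of the sequence handles them. Evaluators, therapists and analyst are blinded and the pain scale is marked by the participant. Custody of data is not outcome assessment.
- A reader might want a count of participants lost after allocation. The documents give no rate for failed examinations or refusals, so any count would be an assumption.

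**Conclusion.** The concern holds in a limited form. Two things are stated: one physiotherapist decides the telephone screen and also creates and runs the sequence, and the number that fixes the arm is tied to passing that screen. From these it follows that, as written, the next assignment is available to the recruiter and that exclusions or refusals can occur after allocation, contrary to the intention-to-treat commitment.

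Whether either has an effect in practice depends on the actual order of steps and on any unpublished safeguard. The abstract and parts of Randomization and blinding suggest a later assignment, and the sections must be reconciled. No bias can be quantified from the documents; the scale is only that of a trial with 18 per arm. The point merits correction because it concerns a procedure that the article fixes, and because changing that procedure is cheap.

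**What to change.** In Randomization and blinding, replace assignment on passing the phone screen with the following order, and align the abstract, Design and Participants with it.

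1. Telephone screen, then signed consent, then the trigger-point examination. State that the examination is completed before the examiner can know the arm.
2. Only then assign the next table number and release the team (G1 or G2). The team has to be known here because it determines the baseline evaluator, so the whole number cannot simply be withheld until after baseline.
3. Keep the arm (A or B) in sequentially numbered, sealed opaque envelopes prepared by someone who neither screens nor examines participants.
4. After the baseline assessment, the needling physiotherapist opens the envelope at the start of session 1. The sentence about a named list of arms has to be changed to fit. Arms already released should stay with that physiotherapist, since balance within blocks lets earlier arms help to deduce later ones.

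The cost is the preparation of envelopes and the separate release of team and arm. All seven listed physiotherapists already have roles, and most must stay blinded or away from the list, so preparing the envelopes probably needs brief help from someone outside that team. The visit at which the examination takes place is not stated and should be named.
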